### Participants

#### Primary care practices

Seventy primary care practices will be recruited from practices in the Netherlands who voluntarily apply to start the practice accreditation program. An invitation letter for the study will be sent as part of the instruction manual for the program. Practices with a clear preference for a specific improvement plan will be excluded from participation in the study while participating practices will be randomized to a group which starts with an improvement plan on CVRM or to a group that does not. This also accounts for practices that participate in regional programs for enhancing disease management.

#### Patients

The study focuses on patients with established CVD. This includes patients with angina pectoris, acute myocardial infarction in their medical history, other chronic ischemic heart diseases, transient ischemic attack (TIA), ischemic stroke, peripheral arterial disease, and aneurysma aortae. Selection of patients out of electronic medical records with these conditions will be based on corresponding diagnostic International Classification of Primary Care codes (ICPC-codes K74, K75, K76, K89, K90.3, K92.1 and K99.1), a worldwide system to label conditions in primary care [18].

#### Randomization

General practices will be the unit of randomization. A computer list of random numbers will be generated by an independent statistician and then used to randomly allocate practices to equally sized intervention group or control group. This will be done in a randomized block design in blocks of four practices in order of enrolment. We assume that improvement activities in the control group will not influence cardiovascular care.

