#### Intervention group

The intervention starts with volunteering for the practice accreditation program. After enrolment for the study, practices will be contacted by telephone for further explanation of the study protocol and to schedule the data collection. After data is collected, practices are randomized. Practices allocated to the intervention group are instructed to focus their improvement plans on cardiovascular diseases in the first year of the program.

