#### Time frame of the study

The study is planned from September 2008 until September 2012. In months 1 to 18, practices are recruited and included in the project and go through the accreditation procedure. The baseline data collection will take place in these months. During months 3 to 42, practices (in the intervention group) work on improving their management of CVD, practices in the control group on improvements in other areas. In months 18 to 42, follow-up measurements in intervention and control practices are planned. During months 43 to 48, data will be analyzed and reported.

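### Fixed blocks of four in enrolment order could let someone who knows the block size and the earlier allocations deduce at most about a third of practice allocations; varying block sizes are a cheap improvement

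*Protocol article*

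**What the plan says.** All references are to the protocol article.

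- **Randomization.** "General practices will be the unit of randomization". "A computer list of random numbers will be generated by an independent statistician", and this list is "used to randomly allocate practices to equally sized intervention group or control group". The scheme is then fixed: "This will be done in a randomized block design in blocks of four practices in order of enrolment".
- **Intervention group.** Practices enrol, are telephoned and have baseline data collected. "After data is collected, practices are randomized". The arm is then disclosed by its content: "Practices allocated to the intervention group are instructed to focus their improvement plans on cardiovascular diseases in the first year of the program". The Control group section gives the mirror-image instruction.
- **Primary care practices (under Participants).** "Practices with a clear preference for a specific improvement plan will be excluded from participation in the study".
- **Time frame of the study.** "In months 1 to 18, practices are recruited and included in the project and go through the accreditation procedure". Entry is therefore spread over up to 18 months.

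The article does not say who holds the list, how allocations are released, or whether those who enrol practices know the block size.

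**The concern.** A permuted block of known size uses itself up. Once both places for one arm are filled, the remaining places are known. Masking the recipients cannot hide past allocations here, because each practice is told what to work on. Having an independent statistician generate the list protects the list itself, but not against inference from what has already been allocated.

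This deserves attention because one exclusion criterion concerns the very thing being allocated: whether a practice clearly prefers a particular improvement plan. If the next arm could be inferred, a practice inclined towards cardiovascular work could be treated as having no clear preference when the next place is intervention, and as having one when it is control. Intervention practices would then tend to be more motivated for cardiovascular care. Practice motivation is not among the factors named for adjustment in Other measures or Statistical methods. Reasons for participating are asked about only in the process-evaluation interviews, so adjustment would not reliably remove such selection.

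**Working it through.** **Inputs.** Block size 4 in enrolment order, equal arms, hence 2 + 2 (Randomization); 70 practices in total and 35 per arm (Sample size); recruitment in months 1 to 18 (Time frame of the study). For power: 55% against 65%, alpha 0.05 (two-sided assumed), power 0.80, ICC 0.05, 30 patients per practice.

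**The plan's own figure.** The article gives no figure for predictability. Its sample size reproduces: 376 patients per arm without clustering; design effect 1 + 29 × 0.05 = 2.45; 376 × 2.45 / 30 = 30.7, rounded up to 31 practices per arm. An allowance of about 11% for dropout (1 − 31/35) gives 35.

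**Certain allocations, fixed blocks of four.** There are 6 possible 2 + 2 sequences.
- Places 1 and 2 are never certain.
- Place 3 is certain only if the first two match: probability 1/3.
- Place 4 is always certain.
- Per block: 1/3 + 1 = 4/3, and (4/3)/4 = 33.3%.
- 70 practices make 17 full blocks plus 2 practices: 17 × 4/3 = 22.7, and 22.7/70 = 32.4%.

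**Best-guess accuracy, fixed blocks of four.** The chances of a correct guess at places 1 to 4 are 1/2, 2/3, 2/3 and 1. They sum to 2.833 per block, or 70.8%. Over 70 practices: (17 × 2.833 + 1/2 + 2/3)/70 = 70.5%, against 50% with no information.

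**These are ceilings.** They assume an observer who knows the block size and sees every earlier allocation in the block before the next practice enters. As an illustration, suppose enrolment is even over 18 months and the lag L from enrolment to randomisation is constant. The gap between enrolments is then g = 18/70 = 0.26 months. At the moment a practice enrols:
- L below g: all earlier block members are already allocated, so the ceiling of 4/3 per block applies.
- L between g and 2g (0.26 to 0.51 months): only place 4 can be certain, and only if the first two match. That is 1/3 per block, or 8.3%.
- L above 2g (0.51 months): none is certain.

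The article does not give L. A longer lag closes the route at enrolment; an exclusion made between enrolment and randomisation would remain possible. If all four members of a block are allocated together, the certain share is zero.

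**Varying block sizes.** Simulation of 3,000 lists of 70, with an observer who knows all past allocations and the set of possible sizes, but not the size of each block:

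| Scheme | Certain, of 70 | Certain, % | Best guess correct |
|---|---|---|---|
| Fixed 4 | 22.7 | 32.4 | 70.5% |
| Random 4/6 | 4.0 | 5.7 | about 69% |
| Random 2/4/6 | 2.9 | 4.1 | about 70% |
| Random 4/6/8 | 1.6 | 2.3 | about 68% |

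**Balance and power.** Since 70 is not a multiple of 4, the fixed scheme itself ends 36/34 in one list of three (the last two practices match); random 4/6 does so in about 23%. Power under the plan's assumptions is 84.9% at 35/35, 84.9% at 36/34 and 84.8% at 37/33.

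**The case against.** The strongest reply is that the one-third figure describes an observer the article never places in the trial. It does not say that recruiters know the block size or see past allocations. Concealment and release procedures are commonly left to a full protocol, which is not shown, and may already be in place. This stands: the figure is a ceiling, and the missing detail is not a fault of the article.

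Several stronger readings are tempting and are not supported:

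- **That staff have several points at which to influence entry.** The telephone call comes after enrolment, so it is not an entry step. Practices apply voluntarily and are invited through the program's instruction manual; no recruiter is described as choosing among candidates. Only the preference exclusion leaves room for judgement, and it may rest simply on what the practice says.
- **That the Randomization and Intervention group sections contradict each other.** They do not. Enrolment order can fix the queue while randomisation follows baseline data collection. That delay lowers predictability.
- **That baseline data are compromised.** They are collected before the practice's own allocation. The planned model includes measurement moment and identified baseline differences, so imbalance in measured factors would be visible and modelled. Unmeasured motivation would not be.
- **That varying block sizes cure the problem.** They remove most certain predictions but leave best-guess accuracy almost where it was for an observer who knows the possible sizes.

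Permuted blocks of four are also a conventional choice. What remains is that the article states a single fixed size, and a less predictable scheme is available for very little.

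**Conclusion.** The point holds as a cheap improvement. Fixed 2 + 2 blocks in enrolment order, in a trial where practices know their arm, allow at most about 23 of 70 allocations (32%) to be deduced. This requires knowledge of the block size and of all earlier allocations in the block before the next practice is admitted or excluded. The true share may be much lower and could be zero, depending on the lag to randomisation and on whether blocks are allocated together.

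A reader might infer that a third of allocations will in fact be known in advance, or that the comparison is biased. The article supports neither. It shows a possible route through the preference exclusion, not that anyone would use it, and the size of any bias cannot be computed from what is given. The sample size is unaffected.

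**What to change.** Either of two changes would do:

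1. Replace the fixed block of four with randomly varying block sizes, for example 4 and 6, and do not disclose the sizes to those who enrol practices.
2. Keep blocks of four, but allocate each complete block together once eligibility and baseline data for all four practices are locked.

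Under the first option, keeping upcoming allocations and block sizes concealed matters as well, because varying the sizes hardly lowers best-guess accuracy. If the full protocol already provides for concealment, only the block size needs changing.

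The first option costs a new list from the same statistician and a possible interim imbalance of three practices instead of two (half the largest block: 6/2 against 4/2). Power is essentially unchanged. Under the second option, practices that are ready early wait until their block is complete.

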#### The practice accreditation program

The practice accreditation program is an existing procedure provided since 2005 by an independent body (NPA) that has a license to use the accreditation procedure developed by the DCGP. The DCGP remains responsible for the content and further development of the procedure; it will be responsible for adequate delivery of the practice accreditation program in this study. The practice accreditation program comprises, firstly, of a comprehensive audit (using validated performance indicators) and written feedback to the practice, which covers a range of clinical domains (mainly chronic diseases), practice management, and patient experiences. The feedback, which consists of a comparison with benchmarks of other primary care practices, is discussed with a non-physician observer in a feedback consultation and helps to identify substandard performance. The second obligatory component, the planning of improvements in the practice according to the principles of quality management, is based on this feedback. The practice team is supported by a trained non-physician consultant. Practices that perform the procedure as planned are all accredited, so accreditation does not imply that a certain minimum score has been obtained (the latter is usually labeled certification). In the practice accreditation program, validated instruments are used: the Visit Instrument to asses Practice management (*Visitatie Instrument Praktijkvoering*, VIP) [19], clinical performance, and Europep [20]. Practices in the program receive a reimbursement of some insurance companies consisting of a bonus per patient per year. Furthermore they receive a certification for the time period of one year that demonstrates (to the public) their involvement in continuous quality improvement. Every year the practice will be audited, and every year new improvement plans have to be formulated that have to be approved by the auditor.

#### Intervention group

The intervention starts with volunteering for the practice accreditation program. After enrolment for the study, practices will be contacted by telephone for further explanation of the study protocol and to schedule the data collection. After data is collected, practices are randomized. Practices allocated to the intervention group are instructed to focus their improvement plans on cardiovascular diseases in the first year of the program.

#### Control group

The control group also starts with volunteering for the practice accreditation program and follows the same routine as described for the intervention group. Practices allocated to the control group are instructed to focus their improvement plans on other domains than cardiovascular disease and diabetes mellitus (they may target CVD later after the study period of one year). They are instructed to focus their improvement plans on other clinical areas than CVD or diabetes.

Both intervention and control group receive feedback on CVD indicators as part of the normal practice accreditation program. Practices in the intervention group are instructed to set targets related to process and outcomes of cardiovascular care (and not just focused on improvement of registration of cardiovascular disease in the medical record system). All practices will receive a minimum of four hours of support by outreach consultants for no cost, which is available in all regions. Also, the practices are provided with examples of improvement plans, which saves time and would make study participation more attractive.

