**Methods/design:**

We have planned a two-arm cluster randomized trial with a block design. Seventy primary care practices will be recruited from those who volunteer to participate in the practice accreditation program. Primary care practices will be the unit of randomization. A computer list of random numbers will be generated by an independent statistician. The intervention group (n = 35 practices) will be instructed to focus improvement on cardiovascular risk management. The control group will be instructed to focus improvement on other domains in the first year of the program. Baseline and follow-up measurements at 12 months after receiving the accreditation certificate are based on a standardized version of the audit in the practice accreditation program. Primary outcomes include controlled blood pressure, serum cholesterol, and prescription of recommended preventive medication. Secondary outcomes are 15 process indicators and two outcome indicators of cardiovascular risk management, self-reported achievement of improvement goals and perceived unintended consequences. The intention to treat analysis is statistically powered to detect a difference of 10% on primary outcomes. The economic evaluation aims to determine the efficiency of the program and investigates the relationship between costs, performance indicators, and accreditation.

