#### Measures of costs

In follow-up measurements items of use of healthcare will be extracted from the medical records with a retrospective three-month observation period. These items include number of contacts in the practice (face to face, telephone, email), use of various types of cardiovascular medication, use of hospital care or other care providers for cardiovascular diagnosis or therapy. Additional information will be collected with patient questionnaires, particularly on other healthcare use (*e.g.*, home care) and productivity losses, using a one-month retrospective observation period. Also, at follow-up in both groups, time and other resources of practice teams spent on quality improvement in the total period of 18 months will be documented. Data-collection on performance indicators will be done in the follow-up measurement by medical record audit.

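### The instruction that separates the arms runs for an unanchored year that is not tied to the outcome audit, and the protocol's own timings for the two conflict

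*Protocol article*

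**What the plan says.** The protocol article gives the duration of the domain instruction in three places.

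- Abstract, Methods/design: "The control group will be instructed to focus improvement on other domains in the first year of the program".
- Intervention group: practices are "instructed to focus their improvement plans on cardiovascular diseases in the first year of the program".
- Control group: CVD and diabetes are off limits, but "they may target CVD later after the study period of one year". No start is given for that year.

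The outcome audit is timed separately. The Abstract places "follow-up measurements at 12 months after receiving the accreditation certificate". According to the Background, the certificate is issued only once the procedure has been performed.

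Three other sections bear on the interval.

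- Measures of costs: at follow-up, "time and other resources of practice teams spent on quality improvement in the total period of 18 months will be documented".
- The practice accreditation program: "every year new improvement plans have to be formulated that have to be approved by the auditor".
- Time frame of the study: recruitment and accreditation take place in months 1 to 18, and "In months 18 to 42, follow-up measurements in intervention and control practices are planned". The same section has intervention practices working on CVD and control practices on other areas throughout months 3 to 42, with no release after a year.

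**The concern.** Both arms enter the accreditation program and both receive feedback on CVD indicators. What distinguishes them is the topic assigned to the improvement plan, so the comparison is protected only while that assignment holds. The assignment is written for a year, the outcome is measured at a point counted from a later event, and nothing links the two. With new plans due every year and CVD feedback already in hand, CVD is an obvious second-cycle topic for a control practice.

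If a control practice starts such a plan before its audit, its outcomes move toward those of the intervention arm. The Randomization section's assumption that control activities leave cardiovascular care untouched then no longer holds. An intervention practice that changes topic early could weaken the contrast from the other side. All three primary outcomes would be affected, and a real effect could be missed.

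**Working it through.** **1. How long is the gap?** Let x be the months from the start of the instructed year to the certificate. The audit falls at x + 12 months and the instruction ends at 12, so the unprotected gap is x.

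- *Year counted from program start.* The Intervention group section says "The intervention starts with volunteering for the practice accreditation program"; data collection and randomization follow, and the certificate needs the completed procedure, so x is above zero. If the 18 months in Measures of costs run from program start to the audit, x = 18 − 12 = 6 months.
- *Year counted from allocation or from the first plan.* The gap lies between 0 and about 6 months.
- *Year counted from the certificate.* x = 0. There is no gap if the audit is on time, but the release falls on the day the audit is due, so any delay is unprotected.

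The 18 months is a costing period. No section states it as the audit date, so 6 months is an inference. The timetable is compatible with it: a practice enrolled in month 1 and audited at the earliest date, month 18, has been in the study for 17 months.

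**2. The plan's own sample size.** Inputs from Sample size: 55% against 65%, power 0.80, alpha 0.05 (taken as two-sided), ICC 0.05, 30 patients per practice.

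- Patients per arm without clustering: [1.960·√(2·0.60·0.40) + 0.842·√(0.55·0.45 + 0.65·0.35)]² / 0.10² = 375.6, so 376.
- Design effect: 1 + 29 × 0.05 = 2.45.
- Practices per arm: 376 × 2.45 / 30 = 30.7, so 31, as stated.

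**3. Cost of dilution.** Let d be the share of the 10-point effect that the control arm as a whole gains before the audit. Then the control proportion is pC = 0.55 + 0.10·d and the contrast is 10(1 − d) points. With k practices per arm, the effective n is k × 30 / 2.45, which is 379.6 for k = 31 and 428.6 for k = 35. With p̄ the mean of the two proportions,

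power = Φ{[(0.65 − pC)·√n − 1.960·√(2p̄(1 − p̄))] / √(pC(1 − pC) + 0.65·0.35)}.

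For d = 0.10 and k = 31: (0.09 × 19.48 − 1.355) / 0.688 = 0.58, so power is 0.72.

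| d (assumed) | Contrast, points | Power, 31 per arm | Power, 35 per arm |
|---|---|---|---|
| 0 | 10.0 | 80.4% | 84.9% |
| 5% | 9.5 | 76.4% | 81.2% |
| 10% | 9.0 | 71.9% | 77.0% |
| 20% | 8.0 | 61.8% | 67.1% |
| 25% | 7.5 | 56.4% | 61.6% |

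d is the share of controls taking up CVD multiplied by the fraction of the full effect they reach by the audit. For example, 20% × 50% gives d = 10%, and 50% × 50% gives d = 25%. The documents give neither factor. The table covers control crossover only; topic change in the intervention arm is not quantified.

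**The case against.** The strongest reply is that the plan already keeps the arms apart. Time frame of the study holds both arms to their topics through month 42, the end of the follow-up window. The one-year study period in the Control group section can be read as the year from certificate to audit, which matches the one-year life of the certificate and leaves no gap. No section says that the year is counted from volunteering, and no domain instruction can exist before randomization. This stands in part. A reader might infer that the protocol openly permits crossover before the audit. It does not: one section releases controls after a year and another gives no release, so the text is in conflict. The favourable reading still has to contend with the Abstract's first year of the program, and it leaves nothing in reserve if an audit is late.

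A reader might also take month 42 to mean audits up to 42 months into a practice. It is a project-calendar limit. Practices accredited by month 18 fall due by month 30, and one that enrolled in month 18 and took 6 months to certify would fall due by month 36. The window to month 42 shows slack in the schedule. It does not show that any audit will be late.

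Finally, a reader might conclude that the planned power is not delivered. That follows only under assumed crossover. The trial also recruits 35 practices per arm, and the calculation takes no credit for baseline adjustment.

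The interviews described under Other measures and Process evaluation ask about other improvement activities and about how plans were composed. They may detect crossover but cannot prevent it.

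**Conclusion.** The sections on the duration of the instruction and the timing of the audit do not agree and need to be reconciled. Depending on where the year starts, protection ends between about 6 months before the audit and the day it falls due. The 6-month figure assumes that the 18 months in Measures of costs run from program start to the audit. Crossover by controls within that interval would bias the contrast toward no effect.

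How much crossover would occur cannot be derived from the documents. If controls gained 10% to 25% of a 10-point effect, power would be about 72% to 56% with 31 practices per arm, or 77% to 62% if all 35 are retained. If there were no crossover, the plan's power would stand. The point is a cheap safeguard for the comparison and does not show that the trial is underpowered.

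**What to change.** - In the Abstract, Intervention group and Control group sections, replace the unanchored year with an instruction, in both arms, that lasts until that practice's follow-up audit is complete.
- State one follow-up interval with an allowed window, and bring the 12 months in the Abstract, the one year in Control group, the 18 months in Measures of costs and the calendar in Time frame of the study into line with it.
- Record the start date of any CVD plan begun in a control practice before its audit. The planned interviews can carry this question.

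The cost is wording and scheduling. A control practice that wants a CVD plan may have to wait until its audit is done. The sample size stays at 31 practices per arm, 35 with dropout.
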